### Participants

Subjects will be recruited via flyers, referrals from local HIV clinics, by word of mouth, or from ongoing studies. Potential research subjects will be screened by telephone or on-site, before being scheduled for a detailed out-patient evaluation at the UH-QMC MR Research Center at the Queen’s Medical Center in Honolulu, Hawaii.

In our pilot studies, we observed effect sizes from 0.7 to 1.2 for pre versus post CWMT in HIV-positive subjects in four of the working memory tests. We will need to enroll ≈ 17 HIV-positive subjects to detect an effect size of 0.7 for 80 % power (two-sided test). Effect sizes for BOLD signal change (pre versus post adaptive CWMT (0 and 1-back)) were 0.58–1.5 in the pilot HIV-positive subjects; at least 26 HIV-positive subjects are needed to detect an effect size of 0.58 for 80 % power (two-sided test). Since we encountered an ≈ 15 % (13 % in HIV and 20 % in the seronegative group) attrition rate in our pilot study, we propose to enroll 30 HIV and 30 seronegative subjects per training group to ensure adequate power, for a total of 120 subjects (60 HIV, 60 seronegative). Based on our experience, we will have to screen ≈ 500 individuals initially by telephone and 200 of these potentially eligible participants in person to have ≈ 150 subjects who will fulfill our study criteria, and complete the baseline evaluation. We expect that only ≈ 120 subjects (60 HIV and 60 seronegative) will follow through and be randomized for the training. We also expect that only 85 % (*n* = 102, 50 HIV and 52 seronegative) will return for the 1 month follow-up and only 80 % of these (*n* = 86, 40 HIV and 42 seronegative) will return to complete the 6-month follow-up evaluations. Furthermore, we expect that ≈ 20 participants who completed the ‘active control’ training will want to continue with the ‘adaptive training’ (Fig. 1).

HIV-infected participants must meet the following inclusion criteria: (1) men or women of any ethnicity, ages ≥ 18 years and able to provide informed consent; (2) HIV seropositive (with documentation from medical records); (3) stable on an antiretroviral regimen for 6 months or will remain without antiretroviral treatment during the duration of the CWMT study.

Seronegative healthy participants must meet the following inclusion criteria: (1) men or women of any ethnicity, ages ≥ 18 years and able to give informed consent; (2) seronegative for HIV (to be confirmed by an HIV ELISA blood test if screened positive with ClearView® COMPLETE HIV-1/2 test).

Exclusion criteria for all subjects are: (1) history of co-morbid psychiatric illness that might confound the analysis of the study (e.g., schizophrenia, obsessive-compulsive disorder, major depression, or bipolar disorder); (2) confounding neurological disorder (e.g., multiple sclerosis, Parkinson’s disease, non-HIV brain infections, neoplasms, cerebral palsy, or significant head trauma with loss of consciousness >30 minutes); (3) significantly abnormal screening laboratory tests (>2 standard deviations) that might indicate a chronic medical condition (e.g., diabetes, severe cardiac, renal or liver disorders) that might affect brain function; (4) medications that could significantly alter functional brain imaging studies; (5) current or history of drug dependence within the previous 2 years, including amphetamines, cocaine, alcohol, and opiates, according to DSM-V dependency criteria (past casual or recreational usage will not be excluded); (6) positive urine toxicology screen (methamphetamine, amphetamine, cocaine, marijuana, benzodiazepine, barbiturates, and opiates except for false positive tests due to medications) on day of neuropsychological testing or fMRI studies; (7) pregnancy (to be verified by urine pregnancy test in women of child-bearing age); (8) inability to read at an 8th-grade level (to be verified by the Wechsler Test of Adult Reading); (9) other contraindications for MRI studies, such as metallic or electronic implants in the body (e.g., pacemaker, surgical clips, or pumps), or severe claustrophobia.

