## Methods/design

The proposed study uses a 2 × 2 repeated-measures analysis of covariance (ANCOVA) design to evaluate the effects of 5 weeks of CWMT, adaptive versus ‘active control (fixed low level)’ training, as assessed by the improvement index (generated from task performances within the CWMT), neurocognitive testing, BOLD-fMRI measurements, cerebrospinal fluid neuroinflammatory proteins, monoamine, and metabolite levels. We propose to enroll 60 HIV-infected individuals and 60 seronegative healthy participants, with 30 adaptive and 30 active-control-training subjects randomized in each group (Fig. 1). HIV-positive and seronegative subject groups will be matched by age, sex, education, socioeconomic status, and cognitive status (matched by global cognitive score from the seven cognitive domains tested), as well as other co-variates (e.g., nicotine smoking and other substances abused). Based on the initial screening evaluations, subjects who fulfill all study criteria will be scheduled for a baseline neuropsychological evaluation, MRI-fMRI scans, and a lumbar puncture.

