### Statistical analysis

All analyses will be performed using SAS, using repeated-measures analysis of variance (ANOVA) as the primary model (co-varied for age and sex). The baseline (initial) values of all key variables will be tested for normality prior to analysis. Appropriate transformations (or non-parametric tests) will be used as necessary. The statistical significance will be determined using a modified Bonferroni procedure for multiple tests [71]. The procedure will have a type I error probability equal to 0.05 for independent tests.

Neurocognitive assessments will be tested using appropriately constructed contrasts within a 2 × 2 repeated-measures ANOVA model. HIV status (and HAND status for subgroup analyses) and training condition (adaptive versus fixed) will be across-subjects variables, and time (baseline, 1-month, 6-months) will be within-subject variables. Analyses will be co-varied for subject age, sex, and other co-variates as needed (e.g., depression scores). Subjects trained in both the adaptive and fixed training will have the training condition as a within-subject variable.

The fMRI time series will be analyzed using Statistical Parametric Mapping software (SPM8, Welcome Department of Cognitive Neurology, UK). After spatial normalization and smoothing, maps of brain activation and differential changes in activation (repeat − baseline) will be calculated for each subject and task, using a fixed-effects model with a block design. In a subsequent random-effects analysis, differences between groups on BOLD signal changes will be evaluated for each task (*t* tests or ANOVA). Statistical significance will be based on cluster-level significance at *P* < 0.05 corrected for multiple comparisons (voxel-level threshold *P* < 0.05, cluster size >100 voxels). Additionally, we will extract regional percentage BOLD-fMRI signals from cubic regions of interest (0.729 cm^3^) centered at cluster maxima, using a customized program written in Matlab. The extracted data will be imported into SAS, where a repeated-measures ANOVA model will be run to confirm and further evaluate the statistical parametric mapping findings.

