## Dissemination plan

At the completion of this trial, we plan to submit several manuscripts to peer-reviewed journals including;‘Neural correlates of adaptive working memory training in HIV patients’: this paper will report on the interim findings from the primary outcome measures, including improvements on working memory performance and neural efficiencies, 1 month and 6 months after the adaptive version of CWMT, to assess the gain and maintenance of working memory improvements after training. Some of the secondary contrast results, including scoring on the Behavior Rating Inventory of Executive Function–Adult Version and *LMX1A* genotype effects, will also be reported. These findings may lead to a larger study to validate whether CWMT can be used as an adjunctive therapy for HAND.‘Computerized working memory training in HIV patients: a double-blind active control study’: this paper will be written at the completion of subject enrollments. We will compare the effects of adaptive versus fixed low level of CWMT on the primary outcome measures, at 1 month and 6 months after training compared with baseline assessments. This will provide further evidence of whether CWMT is effective for working memory and attention deficits in HIV patients.This paper will also report on the findings after the double-blind active control study to evaluate the efficacy of CWMT on the secondary outcome measures, including scores on the the Center for Epidemiological Studies–Depression Scale, Revised, and the Symptom Checklist–90–revised, and ability to conduct activities of daily living (Independent Activity of Daily Living assessment and the Behavior Rating Inventory of Executive Function–Adult Version) before and after CWMT.This paper will report on possible improvements in cerebrospinal fluid neuroinflammatory proteins (chemokines and cytokines) and neurochemicals (dopamine and serotonergic levels and their metabolites) after CWMT. Since only half of the participants might consent to the lumbar punctures, we may need to combine results from the adaptive training group and the fix-low-level training group to evaluate the training effects on these cerebrospinal fluid measurements.

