### Expected findings

#### Gain in working memory performance and transfer of gain to ‘near’ or ‘far’ transfer tasks (Aim 1)

HIV-positive subjects commonly have working memory deficits [3, 23–29, 41–43]. Since working memory is needed to maintain focus on tasks, deficits in working memory may negatively affect many other cognitive domains, and result in HAND. Prior studies of CWMT showed that the program enhanced performance not only on trained working memory tasks, but also on some non-trained visuospatial and non-trained complex reasoning tasks, including executive function [73]. Therefore, we aim to evaluate the efficacy of CWMT on cognitive performance in our subjects.

We hypothesize that all subjects will show improved working memory after Cogmed® RM training (adaptive training > low fixed level ‘active control’ training), both at 1 month and at 6 months after cessation of training. In addition, not only will adaptive CWMT will lead to greater improvements than active control training on the trained tasks, but the gain will transfer to non-trained tasks that require similar working memory processes, including near-transfer tasks (e.g., digit span and spatial span) and far-transfer tasks (e.g., verbal learning, logical memory, short-term memory, and recognition memory). Lastly, we expect that the gain will be greater in subjects with normal cognition (regardless of HIV status) than in those with cognitive deficits (e.g., HAND or HAND-equivalent).

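### The sample size rests on within-group pre-versus-post effects in HIV-positive subjects, so its 80% power does not carry over to the randomised adaptive-versus-control contrast in those subjects

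*Protocol article*

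**What the plan says.** The protocol article, Methods/design, Participants, gives two sizing statements, both for HIV-positive subjects.

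- **Working memory tests.** In the pilot, "we observed effect sizes from 0.7 to 1.2 for pre versus post CWMT in HIV-positive subjects in four of the working memory tests". About 17 subjects are said to be needed at the low end of that range, 0.7, for 80% power, two-sided.
- **BOLD signal.** The pilot effects, before versus after adaptive training, ran from 0.58 to 1.5, and "at least 26 HIV-positive subjects are needed to detect an effect size of 0.58 for 80 % power (two-sided test").

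The section then cites pilot attrition of about 15% (13% in HIV, 20% in seronegative subjects) and settles on 30 subjects per serostatus-by-training cell, presented as sufficient for power. It forecasts 50 HIV and 52 seronegative subjects at 1 month, and 40 and 42 at 6 months.

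Elsewhere the question is between arms:

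- Methods/design: a comparison "with 30 adaptive and 30 active-control-training subjects randomized in each group".
- Statistical analysis: training condition is a between-subject factor.
- Expected findings, Aim 1: adaptive training "will lead to greater improvements than active control training on the trained tasks, but the gain will transfer to non-trained tasks".
- Expected findings, Aim 2: the predicted fall in activation is judged against baseline and also against active control training.
- Dissemination plan, double-blind paper: "We will compare the effects of adaptive versus fixed low level of CWMT on the primary outcome measures".

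**The concern.** A pre-post effect in one trained group and a difference in change between two randomised arms are different quantities. At the same standardised effect, the second needs about twice as many subjects in each arm, because the control arm's mean change must be estimated too. Any gain that the controls also make is subtracted from the effect. The Participants section gives neither a between-arm effect nor a between-arm power, yet it offers 30 per cell as adequate for a trial built around the between-arm question.

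At stake is how an inconclusive adaptive-versus-control result in HIV-positive subjects would be read. A reader of this section would take it as coming from a comparison with 80% power, and the section does not establish that.

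**Working it through.** **Inputs.** From Participants: effects 0.7 and 0.58, 80% power, two-sided; 50 HIV and 52 seronegative subjects at 1 month, 40 HIV at 6 months. From Methods/design: equal allocation, hence 25 HIV per arm at 1 month, 20 per arm at 6 months, and (50 + 52)/2 = 51 per arm pooled at 1 month. The sizing statement gives no alpha; I assume 0.05, in line with "The procedure will have a type I error probability equal to 0.05 for independent tests" under Statistical analysis.

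**Step 1: reproduce the stated sizes as within-group sizes.** Normal approximation for a paired test: n = ((1.960 + 0.842)/d)².

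- d = 0.7: (2.802/0.7)² = 16.02, so 17.
- d = 0.58: (2.802/0.58)² = 23.3, so 24.

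The exact paired t test gives 19 (18 subjects give 79.9%) and 26. The stated 17 and 26 therefore match within-group sizes to within two subjects, although neither variant gives both exactly.

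**Step 2: see where 30 per cell comes from.** 26/(1 − 0.15) = 30.6 and 26/(1 − 0.13) = 29.9. So 30 per cell is about the larger within-group size after attrition.

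**Step 3: size the between-arm contrast.** Normal approximation, two samples: n per arm = 2 × ((1.960 + 0.842)/d)², which is 32.04 (33) for 0.7 and 46.7 (47) for 0.58. The two-sample t test needs 34 and 48 evaluable per arm.

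**Step 4: power at the forecast numbers.** Two-sample noncentral t on change scores, noncentrality d × √(n/2), 2n − 2 degrees of freedom. The whole pilot effect is taken as the between-arm difference (no change in controls).

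| Contrast | n per arm | d = 0.7 | d = 0.58 |
|---|---|---|---|
| HIV, no attrition | 30 | 76.0% | 59.8% |
| HIV, 1 month | 25 | 67.9% | 52.0% |
| HIV, 6 months | 20 | 57.8% | 43.2% |
| Pooled, 1 month | 51 | 93.8% | 82.7% |

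The effect detectable with 80% power at 1 month is 0.81 for HIV-positive subjects and 0.56 pooled.

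**Step 5: sensitivity to control gain.** The documents give no figure for change in controls. Assuming a gain of 0.2 SD, the between-arm effects become 0.7 − 0.2 = 0.5 and 0.58 − 0.2 = 0.38. Power at 1 month is then 41% and 26% for HIV-positive subjects, and about 71% and 48% pooled.

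**Step 6: power for what was actually stated.** For pre-post change in 25 HIV-positive subjects, the paired t test has 92% power at 0.7 and 79% at 0.58.

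**The case against.** Several objections have force.

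*The 80% is delivered for what it describes.* It is attached to pre-post change, where 25 completers give 92% and 79%. Pre-post change is also one of the trial's claims: the Aim 2 prediction refers to baseline as well as to control, and the first planned paper reports gain after adaptive training. This stands. A reader might infer that the trial misses its stated 80%; the documents do not support that. The fault is that the figure is offered as justification for a design whose randomised question it does not address.

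*The pooled contrast is well powered.* The analysis is one 2 × 2 model, and the Aim 1 hypothesis covers all subjects. With no change in controls, the pooled power of 94% and 83% stands, so it would be wrong to call the whole trial underpowered. The limits are that pooling applies HIV pilot effects to seronegative subjects, for whom none are given, and that the pooled figures also fall if controls improve.

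*The standardising SD is not stated.* If the effects are in baseline SD units and the pre-post correlation is about 0.75 (assumption), d becomes d/√(2 × (1 − 0.75)), that is 0.99 and 0.82. A two-arm test then has about 93% and 81% power at 25 per arm and needs 18 and 25 per arm, close to the stated sizes. At a correlation of 0.60, power is 77% and 61%. Baseline adjustment could also help. So 68% and 52% are conditional, and it would be too strong to say that 17 and 26 can only be paired sizes. But the article labels its effects as pre versus post and gives no correlation, so this does not supply the missing between-arm justification.

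*Controls may not improve.* The Neuropsychological evaluation section expects no practice effects on the non-trained working memory tasks. For BOLD, the Aim 2 text cites a one-year study in which attention-network signals rose in HIV-positive subjects, so drift could even widen the difference. Against this, Aim 1 hypothesises improvement in all subjects. The direction is uncertain, and the 0.2 SD gain is only an illustration.

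**Conclusion.** The point holds in a bounded form. The sizing statements are within-group, and the trial's model, hypotheses and main report are between arms. The 80% therefore does not carry over to the adaptive-versus-control contrast in HIV-positive subjects, the only group for which the article gives power.

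The shortfall of 68% and 52% at 1 month (58% and 43% at 6 months) rests on three conditions: standardisation by the SD of change, no change in controls, and two-sided alpha of 0.05 before the modified Bonferroni procedure. The multiplicity procedure would lower these figures, as would any gain in controls. A high pre-post correlation under the baseline-SD reading would raise them.

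A reader might also conclude that the pooled contrast must become primary. The documents do not compel that. It is a trade-off, since the stated main goal is treatment of HAND and half the pooled sample is seronegative.

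**What to change.** Reword the sample-size text in Participants.

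1. Label 17 and 26 as sizes for within-group pre-post change in HIV-positive subjects, and state which SD standardises the effects.
2. Add power for adaptive versus fixed training in HIV-positive subjects, with its conditions: 68% (0.7) and 52% (0.58) at 25 per arm at 1 month, 58% and 43% at 20 per arm at 6 months, detectable effect 0.81 at 1 month.
3. Beside it, give the pooled contrast at 51 per arm, 94% and 83% with no control change. Show the range under an assumed 0.2 SD control gain (pooled about 71% and 48%, HIV-only 41% and 26%), and note that pooling carries HIV pilot effects over to seronegative subjects.
4. Commit to reporting the HIV-positive between-arm difference with its confidence interval, so that an inconclusive result is read by its precision.

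This needs no extra enrolment and no change of primary contrast. The cost is a less favourable stated power for the HIV-positive comparison.

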### Primary and secondary outcome measures

The main goal of this study is to examine the effectiveness of intensive adaptive working memory training for the treatment of HAND. The primary outcome measures will be the improvement index on CWMT, improvement on non-trained near-transfer working memory tasks, and changes on brain activation assessed with BOLD-fMRI during working memory and attention tasks. Secondary contrasts will evaluate genotype effects (*LMX1A*, TT(AA) versus TC(AG) or CC(GG)) on cognitive improvements and BOLD-fMRI. We will also assess CWMT-related improvements on self-reported depressive and various psychopathological symptoms, using the Center for Epidemiological Studies–Depression Scale Revised and Symptom Checklist–90 revised items, and on self-rated functionality, using the Independent Activity of Daily Living assessment and the Behavior Rating Inventory of Executive Function–Adult Version.

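### The claim that 30 per training group ensures adequate power does not hold for the BOLD outcome at 6 months: the plan's own projected completers give about 69 %, and the multiplicity rule is left out of the sizing

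*Protocol article*

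**What the plan says.** All sizing statements are in the Participants section of the protocol article.

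- **Working memory tests.** The pilot effects are within-person: "we observed effect sizes from 0.7 to 1.2 for pre versus post CWMT in HIV-positive subjects in four of the working memory tests". About "17 HIV-positive subjects to detect an effect size of 0.7" are said to give 80 % power in a two-sided test.
- **BOLD signal.** Pilot pre-post effects ran from 0.58 to 1.5, and "at least 26 HIV-positive subjects are needed to detect an effect size of 0.58" with the same power and sidedness.
- **Enrolment.** Pilot attrition was about 15 % (13 % HIV, 20 % seronegative), so "we propose to enroll 30 HIV and 30 seronegative subjects per training group to ensure adequate power".
- **Projected completers.** The same paragraph, and the legend of Fig. 1, expect 50 HIV-positive participants at 1 month and 40 at 6 months, out of 60 randomised.

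The paragraph names no alpha and no multiplicity adjustment. The Statistical analysis section does: "The statistical significance will be determined using a modified Bonferroni procedure for multiple tests", and "The procedure will have a type I error probability equal to 0.05 for independent tests". The section on primary and secondary outcome measures lists three kinds of primary outcome: "The primary outcome measures will be the improvement index on CWMT, improvement on non-trained near-transfer working memory tasks, and changes on brain activation" on fMRI.

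Aims 1 and 2 at the end of the Background, and the predictions for both aims under Expected findings, name 1 month and 6 months as assessment points.

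**The concern.** The paragraph prints a requirement (26), an enrolment figure (30) and projected completer counts that fall below the requirement at both visits. The margin between 26 and 30 absorbs the 13 % HIV loss seen in the pilot, but not the loss that the plan itself projects by 6 months. The required numbers also appear to rest on a plain 0.05, while the analysis prescribes a correction for multiple tests.

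What is at stake is how a null result will be read. With the present wording, a negative BOLD finding at 6 months would be taken as coming from a study with at least 80 % power for the smallest effect it was sized on.

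**Working it through.** **Inputs.** From Participants: d = 0.58 (BOLD) and d = 0.7 (working memory), both pre-post within person; 80 % power, two-sided; 30 HIV-positive per arm; 50 and 40 HIV-positive expected at 1 and 6 months. Assumption: losses fall evenly on the two arms, giving 50/2 = 25 and 40/2 = 20. The printed overall 6-month total of 86 matches neither 40 + 42 = 82 nor 0.80 × 102 = 81.6. The HIV figure is consistent (0.80 × 50 = 40) and is the one used here.

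**Formula.** For a two-sided paired t test, power = P(|T| > t(1 − α/2, n − 1)), where T is noncentral t with n − 1 degrees of freedom and noncentrality d√n.

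**Step 1: reproduce the plan's figures at α = 0.05.**

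- d = 0.58, n = 26: noncentrality 0.58 × √26 = 2.957, critical value 2.060, power 81.1 %. With n = 25 it is 79.5 %, so 26 is the exact paired-t answer.
- d = 0.7: the normal approximation (1.960 + 0.842)²/0.7² gives 16.02, rounded up to 17. The exact t test needs 19; 17 gives 77.3 %.
- A two-sample t test would need 48 and 34 per arm, so the stated figures are single-arm pre-post calculations at an unadjusted two-sided 0.05.

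**Step 2: reproduce the enrolment figure.** 26/(1 − 0.13) = 29.9, so 30. The margin fits the pilot HIV loss. The projected HIV losses are 1 − 50/60 = 17 % at 1 month and 1 − 40/60 = 33 % at 6 months.

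**Step 3: power at the projected completers, α = 0.05.**

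| Visit | n per arm | Critical value | d = 0.58: noncentrality, power | d = 0.7: noncentrality, power |
|---|---|---|---|---|
| 1 month | 25 | 2.064 | 2.900, 79.5 % | 3.500, 91.9 % |
| 6 months | 20 | 2.093 | 2.594, 69.2 % | 3.130, 84.4 % |

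**Step 4: conditional effect of the multiplicity rule.** The documents do not define the testing family. Assume that the three primary outcomes form one family and take the strictest level, 0.05/3 = 0.0167.

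| Visit | n per arm | Critical value | d = 0.58 | d = 0.7 |
|---|---|---|---|---|
| 1 month | 25 | 2.574 | 63.0 % | 81.4 % |
| 6 months | 20 | 2.625 | 50.2 % | 69.1 % |

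Under this assumed family, a stepwise procedure would give power between the values in Steps 3 and 4, depending on the other p-values. With no dropout at all (n = 30), d = 0.58 has 86.7 % at 0.05 and 73.4 % at 0.0167.

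**The case against.** **The sizing is careful in several respects.** It uses the lowest pilot effect for each outcome, 26 is exact, and 30 matches the 13 % HIV loss. At 1 month the unadjusted BOLD shortfall is half a percentage point. All of this stands, and the 1-month BOLD figure alone would not justify a comment.

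**The multiplicity loss cannot be fixed from the documents.** The family is not stated, and a journal article may leave its definition to the full plan. The SPM maps have their own cluster-level criterion, and the regional BOLD analysis in SAS is there to confirm and extend them. This stands too. Figures such as 63 % illustrate one assumption; they are not the power of the study.

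**Crossover participants might add numbers.** About 20 control-trained participants are expected to take up open-label adaptive training and be followed again. Six more HIV-positive completers would bring 20 up to 26. But the sizing paragraph does not count them, the article does not say how many would be HIV-positive, and they would have had control training first.

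**Stronger readings that a reader might infer.**

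- That 30 per arm fails at both visits for every outcome. It does not: for d = 0.7, power is 81 % at 1 month even at 0.05/3, and 84 % at 6 months unadjusted.
- That 26 should be replaced by 35, the number needed at 0.05/3. That would write in an alpha that the article does not state.
- That enrolment was wrongly inflated because 30 × 0.85 = 25.5. This passes over the HIV-specific rate: 30 × 0.87 = 26.1.
- That 17 in place of 19 undermines the design. It is an approximation gap of two subjects, and the larger figure of 26 drives the sample size.

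**Conclusion.** The point holds in a limited form. Taken on the plan's own paired calculation, the adequacy claim is not met for the BOLD effect of 0.58 at 6 months: about 69 % power against the stated 80 %, with no multiplicity assumption needed. It is met to within rounding for BOLD at 1 month, and clearly met for the working memory effect of 0.7 at both visits, when 0.05 is unadjusted.

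That the sizing leaves out the modified Bonferroni rule is certain; how much this costs is conditional. Under one three-outcome family, power would lie between 63 % and 79.5 % (1 month) and between 50 % and 69 % (6 months) for 0.58, and between 81 % and 92 % and between 69 % and 84 % for 0.7.

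These figures assume even losses between arms and the pilot effect sizes. They also accept the pre-post framing, although the hypothesis under Expected findings compares adaptive with active-control training; that is a separate matter, and these figures do not measure power for that comparison.

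**What to change.** In the sizing paragraph of Participants:

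1. State the alpha behind 17 and 26 (two-sided 0.05, unadjusted).
2. Add the power at the expected HIV-positive completers: for 0.58, 79.5 % with 25 per arm at 1 month and 69 % with 20 at 6 months; for 0.7, 92 % and 84 %.
3. Add the adjusted values as a conditional range, with the assumed family named, or define the family so that the range can be replaced by a figure.
4. Limit the statement about adequate power to the outcomes and visits where it holds, and describe the 6-month BOLD analysis as having less than 80 % power for an effect of 0.58.

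The cost is a few sentences. No design change or further enrolment follows from this point. The downside is a less favourable power statement.

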**Fig. 1 Fig1:**
[figure not shown]
Study design. We plan to screen ≈ 500 individuals initially by telephone and 200 of these potentially eligible participants in person, to identify ≈ 150 subjects who will fulfill our study criteria, and complete the baseline evaluation. We expect that only ≈ 120 (60 HIV and 60 seronegative) will follow through and be randomized for the training. We also expect that only 85 % (*n* = 102, 50 HIV, and 52 seronegative) will return for the 1 month follow-up and only 80 % of these (*n* = 86, 40 HIV, and 42 seronegative) will return to complete the 6-month follow-up evaluations. Furthermore, we expect that ≈ 20 participants who completed the ‘active control’ training will want to continue with the ‘adaptive training’. CSF, cerebrospinal fluid; I/E, inclusion or exclusion; MR, magnetic resonance; SN, seronegative; WM, working memory.

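### The 6-month completer count should be 82, not 86, and the 30 per training group allows for no loss after 1 month, so paired power for the smallest pilot BOLD effect in HIV-positive adaptive trainees falls to about 69% at 6 months

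*Protocol article*

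**What the plan says.** The sample-size text is in the Participants section of the protocol article. For the imaging outcome it reports: "Effect sizes for BOLD signal change (pre versus post adaptive CWMT (0 and 1-back)) were 0.58–1.5 in the pilot HIV-positive subjects". From the lower end of that range it concludes that "at least 26 HIV-positive subjects are needed to detect an effect size of 0.58 for 80 % power (two-sided test"). For the working-memory tests it states: "We will need to enroll ≈ 17 HIV-positive subjects to detect an effect size of 0.7 for 80 % power (two-sided test").

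It then cites pilot attrition of about 15%, broken down as "13 % in HIV and 20 % in the seronegative group", and on that basis says "we propose to enroll 30 HIV and 30 seronegative subjects per training group to ensure adequate power". No time point is attached to this claim.

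The same paragraph forecasts follow-up. At 1 month it expects 85% of 120, given as 102 (50 HIV, 52 seronegative). At 6 months it expects 80% of those, given as "86, 40 HIV and 42 seronegative) will return to complete the 6-month follow-up evaluations". The Fig. 1 legend carries the same forecast: "86, 40 HIV, and 42 seronegative) will return to complete the 6-month follow-up evaluations".

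BOLD change is listed among the primary outcomes (Primary and secondary outcome measures). Aim 2 and the expected findings for Aim 2 place it at both 1 month and 6 months.

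**The concern.** Two things do not fit together.

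First, the 6-month total disagrees with its own rate and with its own subgroups. This slip feeds no sample-size calculation, but it makes retention look better than the plan expects.

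Second, the enrolment figure is built from the required 26 with an allowance for a single round of pilot-type attrition. The plan then forecasts a further 20% loss before the 6-month visit, and nothing in the 30 per group covers it. Because the adequacy claim names no visit, a reader will take it to cover 6-month maintenance as well as 1-month gain. If the forecast is right, the plan claims a property at 6 months that its own figures do not give for the smallest effect it planned on.

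A smaller matter sits alongside. The forecast has HIV participants dropping out more than seronegative participants by 1 month, whereas the pilot rates quoted just before run the other way. No reason is given.

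**Working it through.** **Inputs.** From Participants: d = 0.58 with 26 HIV-positive subjects; d = 0.7 with about 17; 80% power, two-sided; pilot attrition 13% (HIV), 20% (seronegative), about 15% overall; 30 per serostatus group per training arm; forecasts of 102 (50 + 52) and 86 (40 + 42). Alpha is not given there; 0.05 is taken from Statistical analysis ("The procedure will have a type I error probability equal to 0.05 for independent tests"). No further multiplicity adjustment is applied.

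**Formula.** The effect sizes are pre versus post, so a paired t-test applies. Power = P(|T| > t₀.₉₇₅,ₙ₋₁), where T is noncentral t with n − 1 degrees of freedom and noncentrality d√n. The normal approximation for n is ((1.96 + 0.84)/d)².

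**1. The plan's own sizes reproduce.**
- d = 0.58: the paired t-test first reaches 80% at n = 26 (81.1%; n = 25 gives 79.5%).
- d = 0.7: the normal approximation gives 16.02, rounded up to 17. The exact t-test needs 19, which is close enough to the approximate figure stated.
- 30 per group: 26/(1 − 0.13) = 29.9, so 30; 26 × 1.15 = 29.9, so 30. Dividing by 0.85 gives 30.6, so 31. The 30 is therefore one round of about 13–15% loss.

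**2. The follow-up counts.**
- 1 month: 120 × 0.85 = 102 = 50 + 52. Reproduces.
- 6 months: 102 × 0.80 = 81.6, and 40 + 42 = 82. The printed 86 does not reproduce; it would be 86/102 = 84.3%.
- Overall retention: 82/120 = 68.3%, against 86/120 = 71.7%.

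**3. HIV-positive completers per arm.** The plan gives HIV totals only, so equal loss in the two arms is assumed.

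| Visit | HIV total | Per arm | Paired power, d = 0.58 | Paired power, d = 0.7 |
|---|---|---|---|---|
| Required for BOLD | – | 26 | 81.1% | 92.9% |
| 1 month | 50 | 25 | 79.5% | 91.9% |
| 6 months | 40 | 20 | 69.2% | 84.4% |

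At n = 20 the noncentrality for d = 0.58 is 0.58 × √20 = 2.594, against a critical value of 2.093. Power reaches 80% at n = 20 when d is about 0.66.

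For scale: keeping 26 per arm at the forecast HIV retention would mean enrolling 26/(50/60) = 31.2, so 32 per arm, for 1 month and 26/(40/60) = 39 per arm for 6 months.

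**4. The group split.** The forecast implies 1-month loss of 10/60 = 16.7% (HIV) and 8/60 = 13.3% (seronegative). The pilot rates would give 60 × 0.87 = 52.2 and 60 × 0.80 = 48, which total about 100 rather than 102.

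**The case against.** Several points on the other side are sound.

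- **The 1-month shortfall is trivial.** It is 25 against 26, a power of 79.5% against 81.1%, and it rests on the equal-split assumption. A reader might infer that the trial is underpowered at 1 month; the figures do not support that.
- **The 26 has a narrow scope.** It is stated for HIV-positive subjects under adaptive training. A reader might infer that every group misses its requirement at 6 months, but the plan sets no such number for seronegative participants or for the active-control arm.
- **Only the lower end of the effect range is affected.** The pilot BOLD effects ran from 0.58 to 1.5. With 20 subjects, power exceeds 80% for any effect above about 0.66, and the working-memory target of about 17 is still met.
- **Crossovers may add data.** About 20 active-control completers are expected to take adaptive training, with follow-up at 1 and 6 months, so 20 is not necessarily the ceiling for a pooled pre-post analysis. But these participants are open-label, their HIV share is not given, and the sample-size text does not count them.
- **The 50/52 split is not shown to be wrong.** The plan never says it was derived from the pilot rates, and it sums correctly to 85% of 120. Additional considerations and future directions reports that pilot participants with HAND dropped out most, which is one possible reason to expect more loss among HIV participants. Replacing the split with 52 and 48 would conflict with the stated 102. What remains is that its rates are unexplained.

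None of this rescues the 86, and none of it supplies an allowance for loss between 1 and 6 months.

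**Conclusion.** The point holds in two parts. The 86 is an arithmetic error, printed twice; 82 agrees with both the 80% rate and the listed subgroups. Separately, the claim of adequate power carries no time limit, yet the enrolment figure allows only for loss up to 1 month. On the plan's own forecast, about 20 HIV-positive participants per arm remain at 6 months, where paired power for d = 0.58 is about 69% instead of the stated 80%, and the detectable effect is about 0.66.

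This rests on equal HIV losses between arms, two-sided alpha of 0.05, the plan's own paired basis, and no credit for open-label crossovers. It concerns the smallest pilot BOLD effect only. It does not show that the trial is too small at 1 month, that the working-memory outcomes lack power at 6 months, or that the forecast split is an error.

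**What to change.** 1. Replace 86 with 82 in Participants and in the Fig. 1 legend.
2. State that the attrition allowance behind 30 per group, and the 80% power for d = 0.58, apply to the 1-month assessment.
3. Add the 6-month figures: about 20 HIV-positive participants per arm assuming equal losses, about 69% power for d = 0.58, and a detectable effect of about 0.66, not counting open-label crossovers. It can be added that power for d = 0.7 remains about 84%.
4. Keep the 50/52 split, but state the rates it assumes (16.7% HIV, 13.3% seronegative) and why they differ in direction from the pilot's 13% and 20%.

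These are text changes with no extra enrolment and no change to the design. The cost is a less favourable stated power at 6 months. Whether to treat the 6-month imaging results as estimation only is the sponsor's choice and is not required by this point.
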